**10.4 Safety Analyses**

Descriptive statistics are mainly used for safety analysis. The incidences of symptomatic intracranial hemorrhage transformation between the groups are described statistically and compared by using the test of χ^2^ or the exact test of Fisher.

According to the relevant regulations of the state, the SAE incidence of the relevant product of the sponsor shall be described.

The vital signs and the laboratory test mesasurements shall be statistically described and compared by using Student's paired t-test and the Wilcoxon signed rank test befoer and after the baseline. The changes of laboratory test results and the ECC indexes are described with cross tabulations before and after the assessment.

**10.5 Pharmacoeconomic analysis**

The cost - utility evaluation methods are used for the pharmacoeconomic analysis of the drug and the sensitivity analysis for the cost and utility indexes.

**10.6 Exploratory Analysis**

For the recurrence rate of stroke and the incidence of dementia after stroke, the case numbers and their percentage shall be described and compared between the groups by using the test of χ2 or the exact test of Fisher. If the difference between groups is statistically significant, the Bonferroni method shall be used to adjust the significance level of α value, and the comparison between the two groups will be conducted further.

The prescription of specific treatment in the acute phase of different TOAST type will be described by listing.

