| **Inclusion criteria** | 1. Age≥18 years 2. In conformity with the diagnosis criteria (draft) of China 2014 Guidelines for Diagnosis and Treatment of Ischemic Cerebral Stroke 3. The onset time of thrombolytic patients are within the time window of thrombolysis 4. The onset time of thrombolytic patients are within one week 5. The patients or legal guardians can understand and sign the informed consent form |
| **Exclusion criteria:** | 1. Cranial CT/MRI can display the presence of cerebral hemorrhage 2. The expected survival time of patients less than three months because of complicated serious systemic diseases i 3. the patients cannot provide continuous follow-up information by investigator judgments |
| **Primary efficacy endpoint** | The proportion of patients with good prognosis (mRS=0-2 points) at 90 days after treatment |
| **Secondary efficacy endpoint** | 1. The proportion of patients with poor prognosis (mRS= 3-5 points) and death (mRS=60 points) at 90 days after treatment 2. The changes in National Institutes of Health Stroke Scale (NIHSS) at discharge from baseline 3. The changes in EQ 5 visual analogue scale (EQ-5D, VAS) at discharge from baseline |
| **Safety parameters** | 1. Incidence rate of symptomatic intracranial hemorrhage transformation during the hospital stay 2. Adverse events 3. Vital Signs 4. Laboratory tests (blood routine test, blood glucose, blood lipids, liver and renal functions, myocardial enzymes, serum electrolytes, and coagulation function) 5. ECG examination |
| **Exploratory analysis** | Analysis on the prescriptions of acute specific treatment for different TOAST types  Stroke recurrence rate and incidence rate of post-stroke dementia at 90 days after treatment |
| **Pharmacoeconomic evaluation** | Calculate the cost/utility of the protocol of combinations of different drugs, and ascertain the optimal protocol of hospital treatment of patients with acute cerebral stroke.  As for the costs, only the direct cost is collected, and the indirect cost and implicit cost are not collected. The quality adjusted life years (QALYs) is adopted for the utility analysis as the health outcome parameter. |

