# Study flow diagram

| **Phase** | **Baseline phase** | **Treatment phase** | | **Follow-up period** | |
| --- | --- | --- | --- | --- | --- |
| Visit | V1 | V2[a](#bookmark) | V3 | V4  (Outpatient or  telephone visit) | V5  (telephone visit) |
| Days | At admission  Day 0 | 7 ± 2 days after administration | At discharge | 90±14 days after administration | 360±28 days after administration |
| Signing informed consent forms | × |  |  |  |  |
| Inclusion / exclusion criteria | × |  |  |  |  |
| Demographic materials and medical insurance type | × |  |  |  |  |
| Visit delay and visits accepted by emergency | × |  |  |  |  |
| Past medical history and risk factors^b^ | × |  |  |  |  |
| Onset and admission^d^ | × |  |  |  |  |
| Glasgow coma score | × |  | × |  |  |
| NIHSS score | × | × | × |  |  |
| mRS score | × |  | × | × | × |
| EQ-5D scale | × |  | × | × | × |
| MMSE scale ^e^ |  |  |  | × |  |
| TOAST classification |  |  | × |  |  |
| Vital Signs^f^ | × | × | × |  |  |
| ECG examination | × |  | × |  |  |
| Laboratory examination^g^ | × |  | × |  |  |
| Imaging examination | × |  |  |  |  |
| Treatment regimen^h^ |  |  | × |  |  |
| Combined medications | × | × | × |  |  |
| Adverse events^i^  Special attention should be paid to the symptomatic intracranial hemorrhagic transformation | At any time | | | | |
| Medical expenses^j^ |  |  | × | × | × |
| Recurrence, survival status and re-admission |  |  |  | × | × |

Note:

1. At visit 2, if the patient is discharged, please directly perform the evaluation related with visit 3.
2. The visit delay, visits accepted by emergency and AIS risk factors are the items that can be evaluated.
3. Past medical history includes: stroke, hypertension, diabetes, dyslipidemia, coronary heart disease, atrial fibrillation, carotid plaques, and history of tumor.
4. Onset and conditions at admission: stroke occurrence time, and main symptoms
5. MMSE scale is only applicable to the patients that receive follow-up visits at 90±14 days after the initiation of administration.
6. The vital signs include body temperature, pulse, respiration and blood pressure. The changes in body temperature 1 day and 24 hours after the onset need to be collected at visit 1.
7. Laboratory tests include: blood routine test, blood glucose, blood lipids, liver and renal functions, myocardial enzymes, serum electrolytes, and coagulation function.

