# 3 Overview of study design

This was a registered, prospective, multi-center clinical study. The study was planned to included 10, 000 patients with acute ischemic stroke (AIS) and record treatment regimens, treatment outcomes and medical expenses during hospitalization in real clinical practice. This study was to collect patients' data through a electronic data capture system (EDC).

According to the recommendations for treatment and follow-up observations in acute phase in the "Guidelines on diagnosis and treatment of acute ischemic stroke in China 2014 (Draft)", the patients with stroke were planed to receive 5 visits, which occurred at admission (baseline assessment, visit 1), 7 days ± 2 days after medication (visit 2), at discharge (visit 3), 90 days ± 14 days after medication (visit 4, outpatient service or telephone follow-up), and 360 days ± 28 days after medication (visits 5, telephone follow-up), respectively. As for the specifics, refer to [Study Flow Chart](#bookmark14).

In the baseline phase, the investigators should verify the inclusion/exclusion criteria, obtain the patients' informed consent, and try to collect the demographic information, past history, onset and admission conditions, and vital signs of the patients; and collect the following data of clinical examination: ECG, laboratory tests (blood routine, blood glucose, blood lipids, hepatic and renal functions, cardiac enzymes, serum electrolytes, coagulation) and imaging findings, and assess Glasgow Coma Scale, NIHSS score, mRS score and EQ-5D Scale. Seven days ± 2 days after medication, the vital signs of the patients were recorded and the NIHSS scores were accessed again. At discharge, the treatment regimen, vital signs, ECG and above laboratory tests results were recorded during hospitalization, and the Glasgow Coma Scale, NIHSS score, mRS score and EQ-5D scale were accessed, and the medical expenses during hospitalization was also collected. On 90 ± 14 days after medication, the recurrence of stroke, survival conditions and re-admissions were collected; the medical expense until this visits since discharge was recorded; and the mRS score, EQ-5D scale and MMSE scale (only applicable for the patients visiting the hospital) were accessed. On 360 days ± 28 days after medication, another telephone follow-up was given again, to ask the patient's health status, access mRS score, EQ-5D scale, and collect medical expenses.

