**7.3 Follow-up period**

**Visit 4(After administration 90 ± 14 days, Outpatient or telephone visit)**

- mRS score
- MMSE scale (Only applicable to the patients that receive follow-up visits at hospitals)
- EQ-5D scale
- Collect medical expenses

The patient's medical expenses from discharge to visit 4 are collected (AIS related medical expense, not including the medical expenses for other diseases), including direct medical cost (including the dug expense, examination expense, laboratory test expense, diagnosis and treatment expense, nursing expense and bed expense due to outpatient service / emergency service / hospitalization) as well as direct non-medical cost (including transportation expense, nutrition expense, family accompanying expense and the expense of auxiliary devices). The above expenses are obtained through the inquiry from the patient and (or) family. Where the expense list cannot be provided, the estimate value verbally given prevails.

- Recurrence

The patient should be inquired about the recurrence, and the date of recurrence and whether the recurrence leads to inpatient treatment should be recorded.

Note: whether the disease recurs is based on the diagnosis of the medical institution verbally told by the patient or his/her cerebral infarction.

The stroke recurrence is defined as: 1) in conformity with the diagnosis criteria of ischemic cerebral stroke; 2) the history of past stroke with clear symptom; 3) infarction foci at different periods verified by cranial CT/MRI[[13]](#bookmark15).

- Survival status

The patients should be inquired about the survival status, and as for the dead patients, it is necessary to record the date and reason of death.

- Re-admission

The patient should be asked whether he/she is re-admitted as well as the frequency and reasons of admission.

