**8.4 Exploratory Analysis**

(1) Analysis of the effects of TOAST typing on specific therapy prescriptions in acute phase of AIS.

(2) Analysis of the relapse rate and the incidence of stroke dementia in three months after treatment.

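### The exploratory dementia incidence rests on one hospital-only MMSE at day 90 with no baseline cognitive test, so it is a prevalence among attenders and its unadjusted comparison can reflect who attended

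*Protocol*

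**What the plan says.** The Abstract lists as exploratory the "Stroke recurrence rate and incidence rate of post-stroke dementia at 90 days after treatment". Section 8.4 restates it as "Analysis of the relapse rate and the incidence of stroke dementia in three months after treatment". Section 10.6 plans that "the incidence of dementia after stroke, the case numbers and their percentage shall be described and compared between the groups", using chi-square or Fisher's exact test, followed by Bonferroni-adjusted pairwise comparisons if the overall test is significant.

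On data collection, the Study flow diagram marks the MMSE at V4 only; the cells for V1, V2, V3 and V5 are empty. Section 3 restricts it: "MMSE scale (only applicable for the patients visiting the hospital". Section 7.3 does the same: "Only applicable to the patients that receive follow-up visits at hospitals". The visit itself is set at "90 days ± 14 days after medication (visit 4, outpatient service or telephone follow-up", so a telephone contact is a permitted way to complete it.

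The baseline scales (Sections 3 and 7.1, flow diagram) are the Glasgow Coma Scale, NIHSS, mRS and EQ-5D. The listed past history has eight items, none of them cognitive. Section 4.2 does not exclude prior dementia. Section 6, however, requires accompanying diseases and concomitant medications, with their indications, to be recorded at the first visit.

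**The concern.** An incidence needs people known to be free of the condition at the start and a way of finding who develops it. Here cognition is tested once, at the end, and only in part of the cohort. Patients followed by telephone and patients who died have no MMSE. What can be calculated is the share of hospital attenders with a low score at about day 90.

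The between-group test adds a second problem. Section 5 leaves the choice of regimen to the doctor, so regimens are likely to differ by site and by severity, and attendance may differ with them. An unadjusted test on attenders can then show a regimen difference that comes from who attended. Section 1 says the study aims to give clinicians a reference for choosing medications, so a dementia incidence by regimen invites reading as a drug effect.

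A statistical analysis plan could supply a cut-off and a denominator. It could not supply a baseline test or scores for patients never tested, because those follow from the protocol's own schedule.

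**Working it through.** **Data sources.** The protocol states no dementia rate, attendance rate or power for this endpoint, so there is no figure to reproduce. The elements compare as follows.

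- *What an incidence needs at baseline:* cognitive status. Available: no test; diagnosed dementia possibly through the accompanying-disease record in Section 6; nothing for undiagnosed impairment.
- *What it needs at day 90:* status of all survivors, with deaths accounted for. Available: MMSE in hospital attenders only. The MMSE as printed in Appendix 5 includes naming shown objects, folding paper and copying a figure, so it cannot be completed in full by telephone.
- *Other sources:* adverse events are not named as a source for this endpoint, and the collection window in flow-diagram note 9 and Section 11.2 closes 30 days after the last administration.
- *Missing-data rule:* Section 10 allows last observation carried forward for efficacy data. A scale measured once has no earlier value to carry.

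**Illustration of the two biases (all inputs assumed).** Let n be the proportion of survivors free of prior impairment who become impaired, and p the proportion with undiagnosed prior impairment. If every survivor were tested, the impaired share would be

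I = p + (1 − p) × n.

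If impaired patients attend with probability 0.25 and others with 0.50, the share among attenders is

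O = 0.25 × I / (0.25 × I + 0.50 × (1 − I)).

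| n | p | I, all tested or equal attendance | O, impaired attend half as often |
|---|---|---|---|
| 10% | 0% | 10.0% | 5.3% |
| 10% | 5% | 14.5% | 7.8% |
| 10% | 10% | 19.0% | 10.5% |
| 20% | 0% | 20.0% | 11.1% |
| 20% | 5% | 24.0% | 13.6% |
| 20% | 10% | 28.0% | 16.3% |

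Worked line: n = 10%, p = 10% gives I = 0.10 + 0.90 × 0.10 = 0.19, and O = 0.0475 / (0.0475 + 0.405) = 0.105. The same true 10% appears as 5.3% to 19.0%; in this worked line the two biases almost cancel.

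**Illustration of the group comparison (all inputs assumed).** Take the same true impaired share, 15%, in two groups, with 1,000 attenders each. With r the attendance of impaired relative to unimpaired patients, O = 0.15r / (0.15r + 0.85).

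- r = 0.5: 0.075 / 0.925 = 8.1%.
- r = 0.7: 0.105 / 0.955 = 11.0%.
- r = 0.8: 0.120 / 0.970 = 12.4%.

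For 8.1% against 11.0%, the difference is 2.9 points with standard error √(0.081 × 0.919/1000 + 0.110 × 0.890/1000) = 1.3 points, a ratio of about 2.2. A two-sided 5% test then declares a difference about 59% of the time. For 8.1% against 12.4% it is about 88%.

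**The case against.** Several stronger statements are tempting, and the documents do not support them.

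- *New and existing cases cannot be told apart at all.* A reader might infer this from the past-history list, but Section 6 asks for accompanying diseases and medications with indications at Visit 1. Diagnosed dementia can therefore be identified if sites comply. Only undiagnosed impairment is out of reach.
- *The reported rate will be too low.* This assumes that impaired patients attend less often. It is plausible but not documented, and undiagnosed prior impairment pushes the figure up. For example, assume that 30–70% attend, that 10% of attenders are impaired and that 20–30% of non-attenders are. The all-patient rate is then 13% (0.7 × 10% + 0.3 × 20%) to 24% (0.3 × 10% + 0.7 × 30%), an understatement of 23% to 58%. The direction is built into those inputs, so the result is not evidence of it.
- *The flow diagram sets a different tested population.* Its note 5 reads "MMSE scale is only applicable to the patients that receive follow-up visits at 90±14 days after the initiation of administration" and omits the hospital. Sections 3 and 7.3 state the restriction, and the scale needs the patient present. The note is loose wording, not a rival rule.
- *Dementia is defined by the MMSE.* The protocol never says so; this is inferred from the absence of any other scheduled cognitive tool. A case definition may properly sit in the statistical analysis plan.

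It is also fair to say that the endpoint is exploratory, that the hospital restriction is openly stated, and that lack of adjustment is not peculiar to this endpoint. These points limit the importance of the matter. They do not make the quantity an incidence or give unattended patients a score.

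**Conclusion.** The point holds as one of labelling, denominator and comparison. The scheduled data support a day-90 prevalence of MMSE impairment among hospital attenders, assuming that the MMSE is the intended basis for the endpoint. They do not support an incidence, and an unadjusted test between freely chosen regimens can reflect attendance. The net direction of bias is unknown and its size cannot be estimated from the documents; the figures above show what is possible under stated assumptions and no more. No primary, secondary, safety or QALY result depends on this endpoint, so the correction is worth making but is not critical to the study.

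**What to change.** - In the Abstract and Sections 8.4 and 10.6, rename the endpoint *proportion with MMSE-defined cognitive impairment at 90 days among patients assessed in hospital*, and drop the word incidence.
- Exclude, or report separately, patients with dementia recorded at Visit 1.
- Report by regimen the number assessed over the number alive, and compare assessed with unassessed patients on baseline and discharge characteristics.
- Make the regimen comparison descriptive, or adjust it for age, baseline NIHSS and site. Add inverse-probability-of-attendance weighting as a sensitivity analysis aimed at all survivors. Weighting handles measured predictors of attendance only and does not supply the missing baseline, so the new name is needed either way.
- Add the hospital restriction to flow-diagram note 5 for clarity.

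The cost is a weaker exploratory claim and a little more analysis. No visit or treatment changes.

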**10.7 Interim analysis**

After starting, an interim analysis will be conduced when a certain number of patients were enrolled; when the data is collected for the data set and entered into the database, the first interim analysis of management is to be conducted, to check whether the required "core" data collection is allowed to perform a meaningfully preliminary data analysis. Then the subsequent interim data analysis is regularly scheduled based on the research progress and the object is the whole database content.

With the approval of Guangdong Techpool Biopharmaceutical Co., Ltd, and the Scientific Recommendation Commission, the data collected in this study may be merged with data from other areas for investigation and analysis in the future. In accordance with applicable laws and regulations, the patients information in the study shall be confidentially managed.

The detailed description of the specific content of of the interim analysis will be provided in the statistical analysis plan (SAP).

The results of the interim analysis will be submitted to the sponsor and the principal investigators by the the co-sponsor (CRO) in the style of statistical analysis report (SAR) and slides.

**11 Reports of Adverse events/ Serious adverse events (AE/SAE)**

In a clinical study, it is extremely important for protecting the patients, investigators and the sponsor by timely, accurately and completely reporting and analyzing the safety information from the clinical study, meanwhile, the sponsor, investigators and the monitor shall fulfill their respective responsibilities in accordance with the Good Clinical Practice (JL No. 3), Adverse Drug Event Reporting and Monitoring Management Methods (WSBL No. 81) and Drug Registration Management Methods (JL No. 28).

Note: this study is initiated by the sponsor (Guangdong Techpool Biopharmaceutical Co., Ltd); in accordance with the sponsor's SOP "Pharmacovigilance Policy", the investigators should submitted the adverse events/serious adverse events/pregnancy events in the patients using the regiterred drug from the sponsor () to Guangdong Techpool according to the protocol and clinical judgement.

**11.1 Relevant Definitions**

Definition and classification of adverse events

**Adverse Event (AE)**

An adverse event (AE) refers to any untoward medical event experienced by patients or subjects after taking the drug, but the event does not necessarily have a causal relationship with the treatment. Therefore, an adverse event (AE) can be any untoward and unexpected signs (including abnormal investigation findings), symptoms or disease that are temporally related to the used (investigational) drug regardless of whether the event is related to the drug.

**Serious adverse events (SAE)**

Serious adverse event (SAE) refers to any adverse medical event that conforms to one or more of the following criteria under any dose:

• Fatal (note: death is the consequence, not the event)

• Life-threatening (Note: "life-threatening" means the patient has the risk of immediate death when the event occurs, and it does not refer to the hypothesis that death will be induced if the event is more serious.

• Causing significant or permanent human wounds and disabilities or organ functional impairment

• Causing deformities and birth defects

• Causing hospitalization or extension of hospitalization time

• Important medical events or needing intervention measures (the above-mentioned circumstances may arise in case of no treatment)

**Causality of events with the investigational drug**

the causality of events with the investigational drug shall be judged by the investigator according to the following criteria:

Definitely related (must meet five of the following criteria)

This category refers to the adverse event that can be determined to be related with the investigational drug. In case of conformity with the following criteria, it can be considered that one adverse event is "definitely related":

1. The occurrence of adverse events and drug application have a reasonable time-dependency.

2. Patient's known disease state, environmental or toxic factors or patient's use of other treatment cannot reasonably explain the adverse events.

3. After dose discontinuation or reduction, the adverse events will disappear or become relieved. (But there are some important exceptions; as for some obviously drug-related adverse reactions, they not disappear even after the drug withdrawal; such as: (1) bone marrow suppression, (2) tardive dyskinesia.)

4. Adverse events are consistent with the suspected drug reaction mode.

5. Adverse events re-occur in case of the re-use.

6. External factors can be ruled out.

